**（4）Recombinant Human Cytochrome P450 Isoenzymes**

The metabolic reaction phenotype of Purinostat Mesylate was determined using in vitro human liver microsomes and recombinant human cytochrome P450 isoenzyme test systems (CYP1A2, CYP2B6, CYP2C8, CYP2C9, CYP2C19, CYP2D6, and CYP3A). The results from the specific chemical inhibition experiments showed that the specific inhibitors for cytochrome P450 isoenzymes (CYP1A2, CYP2B6, CYP2C8, CYP2C9, CYP2C19, CYP2D6, and CYP3A) had no significant inhibitory effect on the formation of metabolite M8, with all inhibition rates being less than or equal to 1.3%. This indicates that CYP1A2, CYP2B6, CYP2C8, CYP2C9, CYP2C19, CYP2D6, and CYP3A play a minimal role or no role in the generation of M8. The recombinant human cytochrome P450 enzyme metabolic experiments indicated that CYP2C19 and CYP3A4 may be involved in the production of the metabolite M8, with relative contribution rates of 31.5% and 35.8%, respectively. Other isoenzymes (CYP1A2, CYP2B6, CYP2C8, CYP2C9, and CYP2D6) played a minimal role or no role in the formation of M8, with relative contribution rates all being less than or equal to 16.6%. Using recombinant enzyme metabolism methods, studies were conducted on CYP3A5, CYP4F2, CYP4F3B, and FMO3. The experimental results indicated that CYP4F2 is involved in the generation of the metabolite M8, while CYP3A5, CYP4F3B, and FMO3 do not play a role in the formation of M8. In summary, the results from both the specific chemical inhibition method and the recombinant human cytochrome P450 enzyme metabolism method suggest that CYP2C19 and CYP3A may be involved in the generation of the metabolite M8, whereas the other isoenzymes (CYP1A2, CYP2B6, CYP2C8, CYP2C9, and CYP2D6) have minimal or no effect on the formation of M8. This indicates that there may be other unknown enzymes participating in the metabolism of Purinostat Mesylate to produce M8 in human liver microsomes and playing a certain role.

# Purposes of the Study

## Primary Purposes

- To observe the tolerability and safety of intravenous administration of Purinostat Mesylate, either as a single or multiple infusions, in patients with hematological malignancies, primarily those related to B-cell tumors (including but not limited to B-cell lymphomas, multiple myeloma, B-cell acute leukemia, T-cell lymphomas, and T-cell acute leukemia) who have relapsed or are refractory to treatment, particularly those who have experienced disease progression after standard treatment or are unsuitable for standard treatment.
- To observe the dose-limiting toxicities (DLTs) of intravenous Purinostat Mesylate in patients with relapsed or refractory B-cell-related hematological malignancies, in order to determine the maximum tolerated dose (MTD) and provide a basis for the dosing regimen in Phase II clinical trials.

## Secondary Purposes

- To evaluate the pharmacokinetic parameters of intravenous administration of Purinostat Mesylate, either as a single or multiple infusions, in patients with relapsed or refractory B-cell-related hematological malignancies.
- To assess the pharmacodynamic indicators of intravenous Purinostat Mesylate after single and multiple infusions in patients with relapsed or refractory B-cell-related hematological malignancies.
- To preliminarily observe the efficacy of Purinostat Mesylate in treating patients with relapsed or refractory B-cell-related hematological malignancies.

# Study Design

## Overall Description of the Study

This study is a single-center, open-label, dose-escalation Phase I clinical trial that employs a conventional "3+3" dose escalation scheme. A total of 21 to 42 patients with relapsed or refractory hematological malignancies primarily associated with B-cell tumors will be enrolled (including but not limited to B-cell lymphomas, multiple myeloma, B-cell acute leukemia, T-cell lymphomas, and T-cell acute leukemia, in cases of disease progression, relapse, or those who are unsuitable for standard treatment after receiving standard treatment protocols). After obtaining informed consent, participants will undergo screening within two weeks prior to the first administration to confirm eligibility and to conduct a series of baseline assessments.

The study is divided into three phases: (1) Single Administration Phase (D1-D7): Eligible participants will be admitted to the hospital on the night before the trial (D0) and will receive an intravenous infusion of Purinostat Mesylate at approximately 8:00 AM the following day (D1). The infusion will be completed within 30 minutes, and participants will be monitored for six days post-administration. (2) Multiple Administration Phase (D8-D25): Participants who complete the single administration phase will proceed to the multiple administration phase. In this phase, doses will be administered on D8, D11, and D15. Participants will be monitored for the occurrence of dose-limiting toxicities (DLTs) and to determine the maximum tolerated dose (MTD). Completion of the multiple administration phase will constitute the main portion of the study. (3) Extended Treatment Phase: After completing the multiple administration phase, participants who tolerate the treatment well and do not experience disease progression, as determined by the investigator, may continue treatment according to the original protocol if it is deemed beneficial. During the extended treatment phase, each treatment cycle will be evaluated by the investigator for tolerability and absence of tumor progression. Based on the tolerability and pharmacokinetic results from other participants in the higher dose groups that have been completed, if no DLTs are observed, participants may be adjusted to a higher dose group for continued treatment until disease progression or intolerable toxicity occurs.

The starting dose will be 1.2 mg/m², and dose escalation will be conducted according to the Modified Fibonacci Scheme, with escalation increments of 100%, 67%, 50%, 40%, 33%, and 33%. Only after completing the single and multiple administration phases of the previous dose group, and based on the tolerability and pharmacokinetic results of that dose group, can a decision be made on whether to proceed to the next dose group, until the maximum tolerated dose (MTD) is established. It is anticipated that the MTD will be determined within seven dose groups, with a maximum sample size projected to be 42 participants.

## Dosing Regimen

### Considerations for the Starting Dose

The starting dose of Purinostat Mesylate will be determined based on a comprehensive evaluation of preclinical in vitro pharmacodynamics, in vivo pharmacodynamics across different species, pharmacokinetic data, and toxicological study results.

**1）Estimation of the Maximum Recommended Starting Dose Based on Toxicology Results**

According to the "Guidelines for the Clinical Trial of Antineoplastic Drugs," for cytotoxic agents, the maximum recommended starting dose (MRSD) can be determined as one-tenth of the maximum tolerated dose (MTD) in rodent studies or one-sixth of the MTD in non-rodent species, expressed in mg/m². For some non-cytotoxic antineoplastic agents, due to their relatively lower toxicity, the starting dose for single administration in Phase I clinical trials can be calculated using one-fifth of the No Observed Adverse Effect Level (NOAEL) from non-rodent studies, or higher.

Based on the MTD calculations, the MRSD should be the value derived from the most sensitive species, which is 3.33 mg/m². From the NOAEL calculations, the MRSD should be less than 1.2 mg/m².

Table 2 Calculation of MRSD Based on MTD from Rodent and Non-Rodent Species

|  | MTD（mg/kg） | Km | HED（mg/m^2^） | MRSD（mg/m^2^） |
| --- | --- | --- | --- | --- |
| Rats | 30 | 6 | 180 | 18 |
| Beagle dogs | 1 | 20 | 20 | 3.33 |

*MTD: Maximum Tolerated Dose，Km: mg/kg Dose conversion to human equivalent dose inmg/m2 Dosing conversion factor，HED: Human Equivalent Dose，MRSD: Maximum Recommended Starting Dose*

Table 3 Calculation of MRSD Based on NOAEL from Non-Rodent Species

|  | NOAEL（mg/kg） | Km | HED（mg/m^2^） | MRSD（mg/m^2^） |
| --- | --- | --- | --- | --- |
| Beagle dogs | <0.3 | 20 | 6 | <1.2 |

**2）Calculation of Pharmacologically Active Dose Based on Preclinical In Vivo Pharmacodynamic Study Results**

The Pharmacological Active Dose (PAD) based on mice is used to predict the minimum dose that may produce the expected pharmacological effect in humans. According to the calculated results, the minimum dose that produces the expected pharmacological effect is 0.75 mg/m².

Table 4 Calculation of MRSD Based on NOAEL from Non-Rodent Species

|  | PAD（mg/kg） | Km | HED（mg/m2） | MRSD（mg/m2） |
| --- | --- | --- | --- | --- |
| Mouse | 2.5 | 3 | 7.5 | 0.75 |

**3）Prediction of Human Clearance Based on Preclinical Pharmacokinetic Results**

Using allometric scaling, combined with preclinical pharmacokinetic results, the clearance rate of the drug in humans is predicted. The calculated clearance rate of the drug in humans ranges from 74.64 to 164.16 L/h.

Table 5 Prediction of the Drug Clearance Rate in Humans Using Allometric Scaling

| **Methods** | **Predicted Human Clearance Rate（L/h）** |
| --- | --- |
| Simple Allometric Scaling | 164.16 |
| Single-Species Allometric Scaling | 96.5（rat） |
|  | 133.90（dog） |
| Two-Species Allometric Scaling | 100 |
| MLP-Corrected Species Scaling (ROE) | 74.64 |
| Multi-Exponential Allometric Scaling | 106.70 |

According to the formula Dose  = CL × AUC× F × 1/SF，where F is the bioavailability (equal to 1 for intravenous infusion) and SF is the safety factor, typically chosen as 10. Based on the NOAEL from preclinical trials in rats and Beagle dogs, along with the predicted human clearance rate using single-species allometric scaling, the calculated starting doses are 1.46 mg/m² and 0.62 mg/m², respectively.

Table 6 Calculation of the Starting Dose Based on the NOAEL from Rats and the Predicted Human Clearance Rate

|  | NOAEL (mg/kg) | AUC (ng.h/ml) | CL (L/h) | Initial dose (mg/m^2^) |
| --- | --- | --- | --- | --- |
| Rats | < 3 | 249 | 96.5 | 1.46 |
| Beagle dogs | < 0.3 | 76 | 133.9 | 0.62 |

*Note: The body surface area for humans is calculated based on a height of 170 cm and a weight of 60 kg, resulting in 1.65 m^2^*

**4）Determination of Starting Dose**

Taking into account the above information and the dose used in Phase I clinical trials of a similar HDAC inhibitor (Panobinostat), which is 1.2 mg/m², the starting dose is determined to be 1.2 mg/m².

### Considerations for Dosing Frequency

In preclinical pharmacokinetic studies, after a single intravenous injection of Purinostat Mesylate in rats, the drug is eliminated quickly, with a half-life of 3.79-6.24 minutes. In contrast, following a single intravenous injection in Beagle dogs, the elimination is slower, with a half-life of 4.49-8.47 hours.

In preclinical in vivo pharmacodynamic studies using a human HCT116 tumor xenograft mouse model, although the plasma half-life of Purinostat Mesylate after a single intravenous injection is only 1.21 hours, the elimination half-life in tumor tissue averages 45.34 hours. Furthermore, after 96 hours, the concentration remains at 0.14 µM, which is significantly higher than the IC50 of Purinostat Mesylate observed in in vitro studies. Additionally, the AUC_0-t_ of the drug in tumor tissue is 74.41 times greater than that in plasma. These results suggest that Purinostat Mesylate can maintain a high level of activity in tumor tissue even 96 hours after administration.

After injecting 5 mg/kg of Purinostat Mesylate into Ighmyc transgenic mice (B-cell lymphoma) and wild-type mice, it was observed that 24 hours later, the drug concentration in the plasma of wild-type mice was undetectable, while the drug concentration in the plasma of Ighmyc transgenic mice was 7.11 ng/mL. Additionally, higher drug concentrations were found in the blood, spleen, and lymph nodes containing a large number of tumor cells, with a longer retention time compared to wild-type mice. Even 48 hours post-administration, the drug concentration remained far above the IC_50_ observed in in vitro studies, and the distribution of the drug in the brain and skeletal muscle was minimal, suggesting a potentially lower risk of neurotoxicity.

Considering the information from preclinical studies and the administration methods of similar HDAC inhibitors in clinical settings (for example, Panobinostat is administered in cycles of 21 days, with four doses given in the first two weeks, where the interval between each pair of doses is no less than 3 days), the current dosing frequency for Purinostat Mesylate is provisionally set to a single administration and continuous dosing on days D1, D8, D11, and D15, with a 10-day interval. Subjects meeting the criteria as assessed by the physician will enter the continuation dosing phase, which consists of administering the drug on days 1, 4, 8, and 11 of each cycle, again with a 10-day interval, for a total cycle length of 21 days. The subsequent dosing frequency may be further adjusted based on the pharmacokinetic and pharmacodynamic results from the first subject.

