| **Drug Administration Plan** | The dosing phase of this study includes three stages: the single-dose phase, the multiple-dose phase, and the extended dosing phase. The pharmacokinetics of the single-dose and multiple-dose administrations are combined, during which safety, tolerability, and preliminary efficacy are observed.  **1. Single-Dose Phase**  The single-dose escalation phase will begin with the starting dose and proceed in an ascending order from low to high doses, with 3 to 6 subjects enrolled in each dose group. In each dose group, 3 subjects will be enrolled sequentially, and a single dose will be administered on Day 1 (D1) at that dose, followed by a 6-day observation period (D2-D7). Each subject will receive treatment with a single dose.  **2. Multiple-Dose Phase**  After completing the pharmacokinetic blood sampling for the single-dose administration, if the subject is well-tolerated, they will enter the multiple-dose phase, with doses administered on Days 8, 11, and 15. Each subject will receive the same dose as in the single-dose phase, with the dose-limiting toxicity (DLT) observation period defined as the first administration to 25 days after the first dose. Initially, only one subject will be enrolled in each dose group to observe their tolerability and safety within the 25 days following the first dose. Only if this subject does not experience a DLT will the remaining two subjects in the same dose group be allowed to enroll simultaneously.  If none of the 3 subjects in a dose group experience DLT, the trial will proceed to the next dose group. If 1 out of the 3 subjects in a dose group experiences DLT, an additional 3 subjects will be recruited to receive the same dose of the investigational drug, and they will be monitored for DLT occurrence.  If 1 DLT occurs among the 6 subjects, the trial will proceed to the next dose group. If 2 or more DLTs occur among the 3 subjects, or if 2 or more DLTs occur among the 6 subjects, the trial will be reduced to the previous dose group. If the previous dose group has fewer than 6 evaluable subjects, an additional 3 subjects will be enrolled to bring the total number of evaluable subjects to 6. If no more than 1 DLT occurs among the 6 evaluable subjects, the trial will be halted, and that dose group will be declared as the maximum tolerated dose (MTD). If the previous dose group has already reached 6 evaluable subjects, the trial will be halted, and that dose will be declared as the MTD.  During the multiple-dose escalation trial, real-time analysis of the pharmacokinetic (PK) data for the selected dose groups will be conducted to determine whether the drug reaches a saturation state in the body based on PK and pharmacodynamic (PD) indicators.  **3. Extended Treatment Phase**  After completing the single-dose and multiple-dose phases, if the efficacy assessment indicates clinical benefit for the subject, they will enter the extended dosing phase. In the extended dosing phase, treatment may continue according to the original dosing regimen or with adjustments to the dose based on the subject's tolerability and existing clinical results. Each dosing cycle lasts 21 days, with doses administered on Days 1, 4, 8, and 11 of each cycle. The number of extended dosing cycles will vary based on the patient's efficacy; subjects who achieve an objective response rate of partial response (PR) or higher after 6 cycles may continue receiving the treatment until disease progression, while those who do not reach PR will discontinue the treatment. Efficacy and safety data will continue to be collected during the extended dosing phase. |

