| Urine routine^d^ | **√** |  | **√** | **√** |  | **√** | **√** | **√** | **√**^#^ | **√** | **√** | **√** |
| Blood biochemistry^e^ | **√** |  | **√** | **√** |  | **√** | **√** | **√** | **√**^#^ | **√** | **√** | **√** |
| Coagulation^f^ | **√** |  | **√** | **√** |  | **√** | **√** | **√** | **√**^#^ | **√** | **√** | **√** |
| M protein^L^ | **√** |  |  |  |  |  |  | **√** | **√**（pre-administration）^m^ |  |  |  |
| Virological examination^g^ | **√** |  |  |  |  |  |  |  |  |  |  |  |
| 12-lead ECG ^h^ | **√** | **√**（Checked once before administration, and 2 hours, 6 hours after administration, as well as on D2 and D7） | | | √（Checked once 2 hours and 6 hours after administration on D8, and once before administration, as well as 2 hours and 6 hours after administration on D11 and D15, and once on D25） | | | | √（Checked once before administration on D1, D11, and D21, and once 2 hours after administration, with additional checks as deemed necessary by the investigator） | | | **√** |
| Radiographic examination^i^ | **√** |  |  |  |  |  |  | **√** |  |  | **√** | **√** |
| Bone marrow examination^n^ | **√** |  |  |  |  |  |  | **√** |  |  | **√** | **√** |
| Echocardiography^j^ | **√** | △ | △ | △ |  | △ | △ | △ | △ | △ | △ | △ |
| Efficacy evaluation^k^ |  |  |  |  |  |  |  | **√** |  |  | **√** | **√** |
| Compliance evaluation |  | **√** |  |  |  |  |  | **√** |  |  | **√** | **√** |
| Adverse events | **√** | **√** | **√** | **√** | **√** | **√** | **√** | **√** | **√** | **√** | **√** | **√** |
| Concomitant medication | **√** | **√** | **√** | **√** | **√** | **√** | **√** | **√** | **√** | **√** | **√** | **√** |

Note: **√** indicates mandatory items, and **△** indicates optional items based on specific circumstances.

The single-dose phase is from D1 to D7, and the multiple-dose phase is from D8 to D25. The DLT observation period is from D1 to D25. If the participant tolerates the treatment well, they may enter the continuation dosing phase on D26.

**BSA Calculation Formula: Dubois-Dubois formulas，BSA = (W ^0.425^ x H ^0.725^) x 0.007184，Weight (kg), Height (cm); The single and multiple doses are calculated based on the weight at the time of the first administration. In the continuation dosing phase, weight is measured again before each cycle. If the weight changes by 10% or more compared to the initial dosing weight, the dosage for that visit will be based on the actual weight. However, the dosage remains unchanged for each cycle.**

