## Definition of MTD

Within 25 days after the first dose, if ≤ 1 DLT occurs among 6 subjects, the highest dose that meets this criterion will be defined as the MTD. If all dose groups specified in the protocol have been completed and no DLT occurs in the highest dose group, then the highest dose will be determined as the MTD.

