## Extended Treatment Phase（D26-）

- Intravenous Infusion Administration: Administered on D1, D4, D8, and D11 of each treatment cycle (21 days).
- ECOG Performance Status: Assessed before administration on D1 of each treatment cycle.
- Vital Signs: Including temperature, heart rate, respiratory rate, and blood pressure (systolic and diastolic); measured within 0.5 hours before each administration, 2 hours after administration, and once on D21.
- Physical Examination: Includes assessments of skin, mucous membranes, lymph nodes, head, neck, chest, abdomen, spine/extremities, and neurological system; conducted once on D1, D11, and D21 of each treatment cycle.
- Laboratory Tests: Conducted once on D1, D11, and D21 of each treatment cycle.
- Complete Blood Count (CBC): Red blood cell count, hemoglobin, platelet count, white blood cell count, neutrophil count, lymphocyte count.
- Urinalysis: Urine protein, urine red blood cells, urine white blood cells.
- Blood Biochemistry: Serum creatinine, urea, total bilirubin, alanine aminotransferase (ALT), aspartate aminotransferase (AST), alkaline phosphatase, total protein, albumin, electrolytes (K+, Na+, Ca2+, Mg2+, Cl-), total cholesterol, low-density lipoprotein (LDL), high-density lipoprotein (HDL), creatine kinase (CK), creatine kinase-MB (CK-MB), alpha-hydroxybutyrate dehydrogenase (α-HBDH), lactate dehydrogenase (LDH), fasting blood glucose.
- Coagulation Function Tests: Prothrombin time (PT), activated partial thromboplastin time (APTT), thrombin time (TT), fibrinogen (FIB).
- M Protein Testing: Conducted prior to administration at the start of the second treatment cycle only for participants with multiple myeloma.
- 12-Lead Electrocardiogram (ECG): PR interval, QRS interval, QT interval, and QTc interval; measured once before administration on D1, D11, and D21 of each treatment cycle, and once 2 hours after administration. Additional tests may be added at the discretion of the investigator if deemed necessary.
- Echocardiogram: Conducted if there are symptoms of cardiac abnormalities such as precordial pain or palpitations, or if deemed necessary by the investigator.

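### The MTD rests on 25 days of D1/D8/D11/D15 dosing, while continued treatment runs on D1/D4/D8/D11 of repeating 21-day cycles; the MTD statement should be limited to the schedule it was observed on

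*Protocol*

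**What the plan says.** **Schedule in the DLT window.** Section 3.2.2 describes "a single administration and continuous dosing on days D1, D8, D11, and D15, with a 10-day interval". The General flowchart fixes the window: "The DLT observation period is from D1 to D25".

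**Schedule afterwards.** The flowchart then says: "If the participant tolerates the treatment well, they may enter the continuation dosing phase on D26". Section 3.2.2 describes that phase as "administering the drug on days 1, 4, 8, and 11 of each cycle, again with a 10-day interval, for a total cycle length of 21" (the unit is days), and Section 6.4 repeats it: "Administered on D1, D4, D8, and D11 of each treatment cycle (21 days").

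**What the MTD is built on.** Section 3.4 defines DLTs within 25 days of the first dose, and Section 3.2.4 bases the decision to move to the next dose group on DLT and safety data from the same 25 days. Section 3.5 defines the MTD by the condition "Within 25 days after the first dose, if ≤ 1 DLT occurs among 6 subjects", without naming the dosing days. The DLT analysis set in Section 10.1 names no extension cycle either.

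**What the MTD is for.** Section 2.1 says the trial is to "determine the maximum tolerated dose (MTD) and provide a basis for the dosing regimen in Phase II clinical trials".

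**How continuation is described.** The Synopsis (Drug Administration Plan) says that "treatment may continue according to the original dosing regimen or with adjustments to the dose", and Section 3.1 likewise refers to the original protocol. Section 3.2.5 allows a subject to escalate in the extension on two conditions. First, the subject has had at least 2 cycles at the current dose, tolerated well and without DLTs. Second, at least 2 evaluable subjects at the higher dose have 25-day data without DLTs.

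**The concern.** The MTD is a statement about a dose given on a particular schedule over a particular time. Here the schedule observed for DLTs includes a 7-day single-dose lead-in and is given once, whereas the schedule on which patients then stay is closer-spaced at the start and repeats. The extension begins the day after the window closes, so a DLT-type event in its first cycle changes neither the dose group's DLT count nor the MTD.

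The MTD is meant to inform the Phase II regimen. If it is quoted without its schedule, a reader may take it as established for the repeating 21-day cycle. Two wording problems add to this. Section 3.2.5 asks for absence of DLTs over extension cycles, a period in which Section 3.4 defines none. The Synopsis and Section 3.1 describe continuation as the original regimen or protocol, although the dosing days differ.

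**Working it through.** **Inputs.** DLT-window dosing days 1, 8, 11, 15, with the window closing on D25 (Section 3.2.2; General flowchart). Continuation dosing days 1, 4, 8, 11 of each 21-day cycle, starting on D26 (Sections 3.2.2 and 6.4; General flowchart).

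**The plan's own figure first.** The stated 10-day interval reproduces for both schedules: 25 − 15 = 10 and 21 − 11 = 10.

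**Counts.** Each row is a direct count of dosing days.

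| Measure | DLT window | Continuation |
| --- | --- | --- |
| Gaps between infusions (days) | 8−1 = 7, 11−8 = 3, 15−11 = 4 | 4−1 = 3, 8−4 = 4, 11−8 = 3 |
| Days spanned by the four infusions | 15 | 11 |
| Most infusions in any 8-day span | 3 | 3 |
| Most infusions in any 11-day span | 3 | 4 |
| Infusions in the first 21 days | 4 | 4 |
| Infusions in the first 25 days | 4 | 6 (days 1, 4, 8, 11, 22, 25) |
| Average infusions per day | 4/25 = 0.160 | 4/21 = 0.190 |

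The ratio of the averages is 0.190/0.160 = 1.19. That figure reflects only the different lengths of the two periods (25/21), because the number of infusions is 4 in each.

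**Reading the table.** Over 8 days and over 21 days the schedules match. The DLT window also contains a 3-day and a 4-day gap in succession (D8, D11, D15), the same pattern as the first three infusions of an extension cycle. What it never contains is the full four-infusion 3/4/3-day pattern, or a second cycle.

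**Routes from extension toxicity to the MTD.**
- Section 3.2.5 and its table act on extension toxicity for the individual subject only.
- Section 3.2.3 lets escalation increments be adjusted on the previous group's safety data without naming a time limit. It does not alter the DLT count or the MTD definition.
- Sections 3.2.4, 3.4 and 3.5 are all tied to 25 days.

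No stated route exists.

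**Reporting.** The safety set in Section 10.1 covers treated patients with at least one safety assessment. Section 10.4 summarises adverse events by dose group with no 25-day cut, so extension events are reported. Because Section 3.2.5 lets subjects change dose in the extension, a summary by dose group does not by itself say which dose a subject was receiving when an event occurred.

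**DLT wording.** Section 3.2.5 requires no DLTs over at least 2 cycles of the extension, while Section 3.4 defines DLTs only up to day 25. Read together, the first condition has no defined content after D25.

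**The case against.** The strongest reply is that the lead-in is a deliberate, disclosed single-dose PK week, and that the density contrast depends on the window chosen. Much of this stands. The 8-day and 21-day counts are equal, both schedules have a 10-day rest, and nothing here asks for the lead-in to be removed.

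A second reply is that Section 3.2.3 allows the dose below the MTD as the Phase II dose. At the top planned step that is 11.2/15 = 0.747 of the MTD, so four infusions on the continuation days total 4 × 11.2 = 44.8 mg/m² over 11 days, against 3 × 15 = 45 mg/m² in the first 11 days at the MTD. Over 25 days the margin no longer covers the difference: 6 × 11.2 = 67.2 against 4 × 15 = 60 mg/m². The provision is also permissive. It softens the concern but does not state which schedule the MTD describes.

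Third, no passage fixes the extension schedule for Phase II, Section 2.1 calls the MTD only a basis, and Section 3.2.2 calls the frequency provisional. That stands, and it is why the point concerns what may be concluded, not which schedule is right.

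Fourth, accumulation was minimal or absent in rats and dogs (Sections 1.4.2.2, 1.4.3.1 and 1.4.3.2). This weakens any presumption of higher risk. It does not settle the matter: in dogs the single-dose MTD was 10 mg/kg and the repeat-dose HNSTD 1 mg/kg (Sections 1.4.2.3 and 1.4.2.4). That comparison is of single with repeated dosing, not of the two human schedules.

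Fifth, the Synopsis follows its reference to the original regimen at once with the correct extension days, so no one should dose on the wrong days because of it. That also stands; the phrase is a wording matter.

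A reader might infer that extension toxicity is dropped from the trial's conclusions. It is not: tolerability after multiple infusions is itself a primary purpose, and Sections 10.1 and 10.4 include those events. What is absent is a link to the MTD.

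**Conclusion.** The point holds in limited form. The DLT count and the MTD rest on D1–D25 with infusions on D1, D8, D11 and D15; continued treatment uses a different, repeating schedule; and Section 3.5 does not say that the MTD is confined to the former. The measured difference is gaps of 7/3/4 against 3/4/3 days and at most 3 against 4 infusions in 11 days, with equal counts over the first 21 days.

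A reader might go further and conclude that the MTD does overstate tolerability on the continued schedule, or that DLT risk rises by some stated amount. The documents do not support either: they give no DLT rates and no comparison of the two schedules, so no change in risk is a possibility alongside an increase. The supportable conclusion is that the MTD may overstate tolerability there.

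The extension data cannot supply a second MTD, because entrants are selected for having tolerated D1–D25 without progression. They can still show descriptively what happens in the first closer-spaced cycle. The conclusion assumes dosing on the nominal days, without visit-window shifts. It is a cheap improvement to interpretation and does not invalidate the design.

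**What to change.** 1. In Section 3.5, and in the reported conclusion, state that the MTD refers to the D1/D8/D11/D15 schedule over 25 days.
2. In Section 10.4, add a descriptive table of extension cycle-1 events of the types listed in Section 3.4, by dose actually received and not by assigned dose group, shown beside the 25-day DLT table. Add a caveat that entrants are selected for tolerating D1–D25 and that the table does not define an MTD. If the statistical analysis plan already specifies such a table, a cross-reference is enough.
3. Reconcile Section 3.2.5, which requires no DLTs during extension cycles, with Section 3.4, which defines DLTs only within 25 days. Reconcile the references to the original regimen or protocol in the Synopsis and Section 3.1 with the stated dosing days.

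Which schedule, dose or decision rule is right is for the sponsor to decide. The cost is protocol wording and one table from adverse-event and laboratory data already collected in the extension, with no extra visits or subjects. The downside is an additional table from a small, selected subgroup, which has to be read with its caveat.
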